### Statistical analysis

The primary analysis will test associations between intensive and conventional vitamin D therapies and observed fluctuations in LF:HF from baseline to 6 weeks later within each treatment block utilizing a non-parametric paired t-test. To further determine the relationships between cardiac autonomic tone and specific vitamin D therapy regimens, we will use a repeated measurements analysis of variance model to account for the cross-over design of the study utilizing Greenhouse-Geisser correction values to account for multiple comparisons. Treatment, treatment period, and treatment sequence will be analyzed as fixed effects within the model, as well as additional effect modifiers (gender, vitamin D, calcium, phosphate, parathyroid hormone). Additional analyses will include a subgroup analysis for those subjects with diabetes mellitus as diabetes has been shown to alter parameters of cardiac autonomic tone and vitamin D metabolism [9,21].

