### Sample size calculation

While we are not aware of any studies examining the use of vitamin D on the primary outcome of this study, previous work by Kontopoulous et al. [47] has demonstrated that post-myocardial infarction (MI) patients (n = 25) randomized to receive 5–10 mg of quinapril (angiotensin converting enzyme inhibitor) per day for 35 days immediately following an MI displayed a 46% reduction in LF:HF from baseline to 6 weeks (mean ± SE: 10 ± 0.7; 5 ± 0.5), while those randomized (n = 25) to receive 50–100 mg of metoprolol per day for 35 days following an MI displayed a similar 36% reduction in LF:HF from baseline to 6 weeks (mean ± SE: 9 ± 0.6; 6 ± 0.4). As such, given that 1) vitamin D deficiency is the norm in hemodialysis patients, 2) vitamin D downregulates the renin-angiotensin system [24,25,35], and 3) increased RAS activity is associated with alterations in cardiac autonomic tone [35-37], we feel there is sufficient justification for the sample size calculation herein**.** Based on these observations, we estimate the standard deviation of the pooled difference in LF:HF from both treatment sequences as 4.53. Using a 2 × 2 crossover design (2 sequences or treatment orderings and 2 time periods or occasions) and anticipating a 20% or larger reduction in LF:HF observed after 6 weeks of treatment with combined vitamin D vs. the reduction observed after 6 weeks of treatment with alfacalcidiol alone, we estimate that 54 subjects will be required (α = 0.05, β = 0.9). In anticipation of a 10% dropout rate, approximately 60 subjects in total will be recruited.

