## Discussion

In summary, the VITAH trial will determine whether an intensive vitamin D supplementation regimen will improve cardiac autonomic tone compared to conventional vitamin D supplementation in patients receiving chronic hemodialysis. As the trial will remain relatively small in nature, it is possible that potential sources of bias may influence the results obtained. For example, subjects recruited must be stable dialysis patients which may represent a different area of the patient spectrum in terms of the benefit that may be derived from vitamin D supplementation therapy. Furthermore, our study is limited to the Calgary, Alberta area in Canada which may play a role in the vitamin D levels of our subject population based solely on geographical location and seasonal sunlight exposure although current evidence would suggest that a majority of dialysis patients are vitamin D deficient regardless of geographical location [24,26-28]. The evidence surrounding the relationship between various vitamin D therapies and cardiovascular risk derived from clinical trials is extremely scarce. The OPERA study by Wang and colleagues [48] has recently demonstrated that in subjects with non-dialysis dependent chronic kidney disease, 52 weeks of daily paricalcitol supplementation did not alter left ventricular mass, volume, or ejection fraction. Critically, the study showed that cardiovascular-related hospitalization rates were significantly reduced in the vitamin D treatment group compared to placebo, suggesting that vitamin D may affect cardiovascular risk and underscoring the need for other cardiac parameters, such as cardiac autonomic tone, to be evaluated in relation to vitamin D supplementation. The VITAH trial will lend much needed data to the literature pool, and moreover conclusions drawn from this trial will provide quality evidence towards the current equipoise which exists within the discussion of the clinical efficacy of vitamin D in reducing cardiovascular-specific risk in this growing vulnerable chronic patient population.

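### The primary paired test ignores period and sequence; a period-adjusted contrast should be primary, although the loss depends on a period effect of unknown size and N = 54 stands

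*Protocol article*

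**What the plan says.** Under Statistical analysis, the primary analysis looks at the change in LF:HF "from baseline to 6 weeks later within each treatment block utilizing a non-parametric paired t-test". The next sentence begins a further analysis: "we will use a repeated measurements analysis of variance model to account for the cross-over design of the study". That later model is where the design terms appear: "Treatment, treatment period, and treatment sequence will be analyzed as fixed effects within the model".

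Under Sample size calculation, power is planned for the crossover, "Using a 2 × 2 crossover design (2 sequences or treatment orderings and 2 time periods or occasions", with this input: "we estimate the standard deviation of the pooled difference in LF:HF from both treatment sequences as 4.53". No allowance for a period effect is mentioned.

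Under Study interventions, patients already taking vitamin D stop it for 4 weeks before the first block and untreated patients start at once. The second block follows a 12-week washout for everyone. Primary outcome takes the change from each block's own baseline (weeks 0 to 6 and 18 to 24).

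**The concern.** In a 2x2 crossover, randomising the order lets a difference between periods be separated from the treatment effect. The analysis has to use the order for that to happen. A paired test on each patient's two changes does not.

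Count a fall in LF:HF as positive. Let τ be the treatment effect (intensive minus conventional) and D the mean change in block 1 minus that in block 2. The expected paired difference is τ + D for patients given intensive therapy first and τ − D for the others. The paired test treats this systematic split as random noise. If the two sequences contribute unequal numbers, part of D also stays in the estimate.

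The washout arrangement gives a reason for D to differ from zero: the first block starts 4 weeks after stopping vitamin D, or with no stop, and the second starts 12 weeks after study drug. At stake are the power and interval width of the primary result, and its agreement with the trial's own crossover model.

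**Working it through.** **Inputs.** From Sample size calculation: SD of the difference 4.53, α = 0.05 (taken as two-sided), power 0.90 (the article prints this as β), N = 54, 10% dropout. The target is a 20% reduction with no absolute value. I assume 2.0, which is 20% of the cited baseline of 10 ("mean ± SE: 10 ± 0.7; 5 ± 0.5"). D is not in the article; I show 0 to 3 units as an assumption. The primary test is read as comparing each patient's intensive change with that patient's conventional change.

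**1. The plan's own figure.** n = (1.96 + 1.2816)² × (4.53/2.0)² = 53.9, so 54; 54/0.9 = 60. Both are reproduced. With 2.0 replaced by 1.8 (20% of the other cited baseline, 9) the two-sided answer would be 67, so 2.0 is the value that fits.

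**2. Balanced sequences, 27/27.** The paired test sees an SD of √(4.53² + D²), while the mean difference still has standard error 4.53/√54 = 0.6165. Example at D = 2:
- SD seen: √(20.52 + 4) = 4.952, so the interval is 4.952/4.53 = 1.09 times as wide as it need be.
- Rejection threshold: 1.96 × 4.952/√54 = 1.321.
- Power: Φ((2 − 1.321)/0.6165) = 0.865.
- Type I error: 2Φ(−1.96 × 4.952/4.53) = 0.032.

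The same steps for each D, with simulated power beside them (10,000 trials per setting, normal differences):

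| D | SD seen | Power, normal formula | Paired t, simulated | Signed-rank, simulated | Type I error, formula | Period-adjusted t, simulated power |
|---|---|---|---|---|---|---|
| 0 | 4.530 | 0.90 | 0.89 | 0.88 | 0.050 | 0.89 |
| 1 | 4.639 | 0.89 | 0.89 | 0.87 | 0.045 | 0.89 |
| 2 | 4.952 | 0.86 | 0.85 | 0.83 | 0.032 | 0.89 |
| 3 | 5.433 | 0.81 | 0.80 | 0.76 | 0.019 | 0.89 |

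The simulated type I error of the period-adjusted test was about 0.05 at every D.

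**3. Unequal sequences.** Bias = D(n1 − n2)/(n1 + n2), with n1 the number given intensive therapy first. At D = 2:
- 26/28: 2 × (−2)/54 = −0.07 units, 4% of the assumed effect.
- 24/30: 2 × (−6)/54 = −0.22 units, 11% of it. Simulated paired-t power is about 0.75.
- 30/24: +0.22 units. Simulated paired-t power is 0.92, on an estimate that is too large.

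The period-adjusted estimate is unbiased in all three, with power near 0.89 in the two 24/30 splits, where it was simulated.

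**4. Price of adjusting when D = 0.** At n = 54 the paired t-test (53 df) has power 0.8897 and the period-adjusted t-test (52 df) 0.8895.

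**The case against.** The case for leaving the plan alone is fairly strong on size.

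- **D is undocumented, and most sources one might name do not produce it.** The outcome is change from each block's own baseline, so a steady drift gives the same change in both blocks and cancels. Patients are also selected as stable. Season is tempting, because the Discussion mentions "geographical location and seasonal sunlight exposure". That sentence concerns vitamin D levels in a single-location population, and recruitment from 2013 to 2016 spreads block 1 over the calendar, so season largely averages out. The unequal run-in to the two blocks is the main source left.
- **The loss is small unless D is large.** At D = 1 it is under one point of power. It becomes material at D = 2, a period effect as big as the assumed treatment effect.
- **The 24/30 split is near-worst.** From 30/30, all six expected dropouts must fall in one sequence. If loss is unrelated to sequence the chance is 2·C(30,6)/C(60,6) = 2.4%. Study withdrawal also plans last observation carried forward, so the analysed set need not be the completers.
- **The period-adjusted model is already prespecified**, so a period effect would be seen.
- **The authors chose a non-parametric test**, and a remedy based only on means would set that choice aside.

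All of this limits the size of the point, and the last item shapes the fix. It does not defend the unadjusted test as primary, which gains nothing material when D = 0. Carrying values forward does not settle the matter either: if both block-2 values were carried forward for a patient who left after block 1, that patient's block-2 change would be zero, itself a difference between periods.

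**Conclusion.** The point holds in a conditional form. The primary test omits period and sequence, so its p-value and interval do not use the crossover structure that the plan's own further model uses. With balanced sequences the consequence is conservative: intervals too wide, type I error at or below 0.05, and power falling from about 0.89 to 0.85 at D = 2 and 0.80 at D = 3. With unequal sequences the estimate is biased in either direction and power may fall or rise.

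Three stronger readings are not supported:
- **The sample size is wrong.** It is not. The plain paired formula gives 54, and the article does not say that 4.53 is a period-adjusted SD.
- **Any period effect costs power.** A 30/24 split at D = 2 raises it.
- **False positives are inflated.** In the balanced case they become rarer.

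The figures rest on an effect of 2.0, normally distributed differences and an assumed D. The defect is modest, but the remedy is nearly free and worth adopting.

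**What to change.** Name a period-adjusted contrast as the primary analysis. For each patient take the block-1 change minus the block-2 change and compare this quantity between the two randomised sequences. Half the difference between sequences is the treatment effect, reported with its 95% CI. Two forms would serve:

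- If a non-parametric test is wanted, use a rank-sum test between sequences with a Hodges-Lehmann estimate and interval, both halved.
- Otherwise use the two-sample t form, or move the already planned model with treatment, period and sequence from further to primary, fitted to the block changes.

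Keep the unadjusted paired test as a sensitivity analysis.

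The cost is a sentence or two in Statistical analysis and about one degree of freedom (power 0.8895 against 0.8897 when D = 0; these are the t-based figures, and the rank-based pair was not computed). No new data are needed, and the targets of 54 and 60 stay as they are.

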### Study design and setting

The VITAH Trial is a 2x2 cross-over, randomized-controlled trial with blinding of subjects, investigators, health care providers, as well as all study coordinators and data analysts. Hemodialysis outpatients from the Southern Alberta Renal Program will be randomized to one of two treatment sequence arms; 6 weeks of intensive vitamin D therapy (0.25 mcg alfacalcidiol at each dialysis session plus 50,000 IU of ergocalciferol once per week and placebo the remaining two weekly dialysis days), followed by a 12 week washout, and 6 weeks of conventional vitamin D therapy (0.25 mcg alfacalcidiol plus placebo at each dialysis session), or vice versa. Twenty-four hour Holter ECG monitors are applied within the first hour of the first weekly dialysis run at baseline and every 6 weeks throughout the entire 24-week duration of the trial (Figure 1). The study protocol will not impact on uremia clearance given that the dialysis prescription will remain constant. Subject recruitment began in January 2013 and will continue until 2016.

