### Primary outcome

The primary outcome of the study is sympathovagal balance (LF:HF), interpreted as the overall balance on stimulatory and inhibitory cardiac autonomic control, from baseline to the final study day within each 6 week treatment block (0 and 6 weeks, 18 and 24 weeks). Comparison of measured sympathovagal balance throughout each of the vitamin D supplementation treatment blocks as well as the 12-week washout period will allow for statistical interpretation of whether presence or absence of oral vitamin D therapy alters cardiac autonomic function within this population. An improvement in sympathovagal balance can be interpreted by a downward shift in LF:HF, in which a smaller value indicates greater contribution of cardioprotective vagal activity (Table 2).

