### Secondary outcomes

The secondary outcomes include additional measures of cardiac autonomic tone, including LF, HF, as well as time domain parameters of HRV including the standard deviation of the normal R-R interval (SDNN), standard deviation of the average normal R-R interval (SDANN), percentage of normal R waves occurring ≥ 50 ms after the R waves immediately before (pNN50%), as well as blood draw measurements related to vitamin D metabolism at the beginning and termination of each 6 week treatment block (Table 2).

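### Greenhouse-Geisser is named as the multiple-comparison adjustment in the further repeated-measures ANOVA, but it corrects only for non-sphericity and gives no family-wise control over the secondary HRV tests

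*Protocol article*

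**What the plan says.** The Primary outcome section names a single primary outcome: "The primary outcome of the study is sympathovagal balance (LF:HF"). The Statistical analysis section tests its change over six weeks "within each treatment block utilizing a non-parametric paired t-test".

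A second analysis follows: "To further determine the relationships between cardiac autonomic tone and specific vitamin D therapy regimens, we will use a repeated measurements analysis of variance model", and this model is to be fitted "utilizing Greenhouse-Geisser correction values to account for multiple comparisons". Its factors are listed next: "Treatment, treatment period, and treatment sequence will be analyzed as fixed effects within the model". Effect modifiers and a diabetes subgroup analysis are then added.

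The Secondary outcomes section says: "The secondary outcomes include additional measures of cardiac autonomic tone, including LF, HF, as well as time domain parameters of HRV". The five HRV measures are LF, HF, SDNN, SDANN and pNN50%; blood measures are listed as well. Study design and setting schedules Holter recordings "at baseline and every 6 weeks throughout the entire 24-week duration of the trial", which gives five visits (weeks 0, 6, 12, 18 and 24). The article names no other multiplicity method.

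**The concern.** Greenhouse-Geisser addresses one problem. When a within-subject factor has three or more levels and the variances of the differences between levels are unequal, the ordinary F test rejects too often. The correction multiplies both degrees of freedom by an estimate ε no greater than 1. It operates inside one F test on one outcome. It does not adjust for testing several outcomes, for pairwise contrasts after the F test, or for subgroups.

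The article therefore states a purpose that the method cannot serve. This is an incorrect statement rather than a detail left to a later document, and an analysis plan that repeated the sentence would carry the error forward.

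At stake are the secondary claims. The Study aims section makes separate sympathetic and vagal effects the secondary aim and expects all autonomic parameters to rise. A reader who meets a secondary HRV result below 0.05, and who has read this sentence, could take it as already adjusted.

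**Working it through.** **1. The plan's own figure.** The Sample size calculation section says: "we estimate that 54 subjects will be required (α = 0.05, β = 0.9"). I read β = 0.9 as power 0.90. The standard deviation of the difference is given as 4.53. The absolute difference is not stated; I assume 2.0, which is 20% of the cited baseline of 10.

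- n = (SD × (z₀.₉₇₅ + z₀.₉₀) / δ)² = (4.53 × (1.960 + 1.282) / 2.0)² ≈ 53.9, so 54.
- With 10% dropout: 54 / 0.9 = 60.

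The stated figure reproduces as a single two-sided test of LF:HF at 0.05. A noncentral t calculation gives 56, with power 0.89 at n = 54. Greenhouse-Geisser does not enter this calculation.

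**2. What the correction does to the named factors.** For k levels, ε lies between 1/(k − 1) and 1.

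- Treatment and period have k = 2, so the lower bound is 1/1 = 1 and ε = 1. There is only one difference between levels and so only one variance; nothing can be unequal. The F test is unchanged.
- Sequence is a between-subject factor, so sphericity does not arise.
- A factor for the five visits has k = 5, so ε can fall as low as 1/4. Here the correction has a use, but visit is not among the fixed effects listed.

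**3. Does each corrected F test hold its level?** This was checked by simulation under the null: 54 subjects, five visits, autoregressive correlation 0.8 between visits (assumed), 4,000 runs per setting. A single Greenhouse-Geisser F test rejected in 4.75% to 4.98% of runs. The Monte Carlo standard error is √(0.05 × 0.95 / 4000) ≈ 0.34 percentage points, so this agrees with 5%.

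**4. Chance of at least one false positive across the five secondary HRV measures.** If they are independent, 1 − 0.95⁵ = 0.226. The same simulation, with every test Greenhouse-Geisser corrected and an assumed common correlation between outcomes, gives:

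| Between-outcome correlation (assumed) | At least one of five below 0.05 |
|---|---|
| 0 | 21.9% (formula: 22.6%) |
| 0.5 | 17.5% |
| 0.8 | 12.9% |

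**5. Visit contrasts.** Five visits give 5 × 4 / 2 = 10 pairwise comparisons. Left unadjusted on one outcome, at least one fell below 0.05 in about 26% of null runs. The corrected overall F test does not alter these comparisons.

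**6. A narrower family.** If the secondary aim is taken to rest on LF and HF alone, the independence figure is 1 − 0.95² = 9.75%.

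**The case against.** The phrase is attached to one supporting model, and the article does not say that it covers every secondary measure. It may be loose wording for repeated measurements over visits, where the correction does have a role. The error rates above are the ordinary rates for unadjusted secondary tests and would be the same if the phrase were deleted. All five measures come from the same Holter recording, so independence is implausible and 23% is an upper bound. No confirmatory status is claimed for the secondary outcomes.

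Most of this stands and limits the point. A multiplicity rule for secondary outcomes may sit in an analysis plan not shown, so its absence alone is no finding. What remains is that a method is named for a purpose it does not serve, and nothing else in the article repairs this.

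A reader might go further and infer that all the HRV tests, the primary one included, run without error-rate control. The documents do not support that. LF:HF is the only primary outcome, it has its own paired test set out before and apart from the ANOVA, and the trial is sized on it at 0.05. Nor does any single corrected F test lose its 5% level. Only family-wise control across the further and secondary tests is missing.

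**Conclusion.** The point holds in this limited form. The Statistical analysis section wrongly gives Greenhouse-Geisser as a multiple-comparison adjustment. For the treatment contrast it does nothing, and across the secondary HRV measures, visit contrasts and diabetes subgroup it offers no family-wise protection. Over five secondary HRV tests the family-wise rate is about 13% to 23% against a nominal 5%. That range rests on assumed between-outcome correlations of 0.8 to 0 and on all five measures being tested at 0.05. The primary conclusion and the sample size stand. The consequence is for how secondary results may be described: they need not be adjusted, but they must not be presented as adjusted when they are not.

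**What to change.** Reword the sentence so that Greenhouse-Geisser is a sphericity correction, used for any within-subject factor with three or more visits. Then choose one of two courses and state it before unblinded analysis:

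- **Apply a real method.** For example, use Holm across LF, HF, SDNN, SDANN and pNN50%, with the primary LF:HF test kept at 0.05. The family-wise rate for those five is then at most 5%. The cost is not trivial: the smallest of the five p-values is multiplied by 5, so 0.02 becomes 0.10, and some secondary results will lose significance.
- **Label the secondary and further tests exploratory.** Report estimates with confidence intervals and make no claim of adjustment. The cost is that no confirmatory secondary claim can be made.

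Either course is acceptable, and Holm is one option among several. Both change wording and analysis only; sample size, visits and trial conduct stay as they are.

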### Sample size calculation

While we are not aware of any studies examining the use of vitamin D on the primary outcome of this study, previous work by Kontopoulous et al. [47] has demonstrated that post-myocardial infarction (MI) patients (n = 25) randomized to receive 5–10 mg of quinapril (angiotensin converting enzyme inhibitor) per day for 35 days immediately following an MI displayed a 46% reduction in LF:HF from baseline to 6 weeks (mean ± SE: 10 ± 0.7; 5 ± 0.5), while those randomized (n = 25) to receive 50–100 mg of metoprolol per day for 35 days following an MI displayed a similar 36% reduction in LF:HF from baseline to 6 weeks (mean ± SE: 9 ± 0.6; 6 ± 0.4). As such, given that 1) vitamin D deficiency is the norm in hemodialysis patients, 2) vitamin D downregulates the renin-angiotensin system [24,25,35], and 3) increased RAS activity is associated with alterations in cardiac autonomic tone [35-37], we feel there is sufficient justification for the sample size calculation herein**.** Based on these observations, we estimate the standard deviation of the pooled difference in LF:HF from both treatment sequences as 4.53. Using a 2 × 2 crossover design (2 sequences or treatment orderings and 2 time periods or occasions) and anticipating a 20% or larger reduction in LF:HF observed after 6 weeks of treatment with combined vitamin D vs. the reduction observed after 6 weeks of treatment with alfacalcidiol alone, we estimate that 54 subjects will be required (α = 0.05, β = 0.9). In anticipation of a 10% dropout rate, approximately 60 subjects in total will be recruited.

